## Abstract

**Background:**

Opioid use and misuse during pregnancy rose from 1.5 to 6.5 per 1000 deliveries between 1999 and 2014 and continues as a significant public health concern. A fivefold increase in neonatal opioid withdrawal syndrome (NOWS) has accompanied the increase in opioid use. The Eating, Sleeping, Consoling care approach (ESC) has been shown to improve outcomes for infants with NOWS and is quickly becoming the standard of care for infants affected by opioid use disorder. Quality improvement initiatives following the implementation of ESC provide some evidence to suggest that symptom-based (i.e., as needed, PRN, just in time) dosing of opioid medications for infants with significant withdrawal may be an effective alternative to using a traditional scheduled opioid taper approach. These initiatives have shown reduced length of hospital stay and decreased postnatal opioid exposure when compared to scheduled opioid dosing for infants with NOWS who receive pharmacologic treatment. It is unknown if the findings from these quality improvement initiatives are generalizable, and little is known about the safety of this approach in a diverse population. The purpose of this manuscript is to describe the design and rationale for an ongoing study to evaluate the effect of symptom-based opioid dosing compared to traditional scheduled opioid taper on short-term outcomes for infants with NOWS.

**Discussion:**

This trial is uniquely and efficiently designed to establish the efficacy, safety, and generalizability of the symptom-based dosing approach to opioid treatment for NOWS.

**Trial registration:**

NCT05980260; registered July 27, 2023.

## Introduction

### Background and scientific rationale

Antenatal opioid exposure may result in neonatal opioid withdrawal syndrome (NOWS). Neonatal opioid withdrawal is characterized by dysfunction in 3 primary areas: (1) the central nervous system, (2) the autonomic nervous system, and (3) the gastrointestinal system. Signs of withdrawal include but are not limited to irritability, tremors, increased tone, hyperthermia, poor sleep, poor feeding, vomiting, and diarrhea. The natural history of NOWS is an initial increase in symptoms as placentally transferred opioids are cleared from the infant’s system. With time, withdrawal symptoms will eventually abate. The therapeutic focus is on the reduction of symptom severity, with a goal of ensuring normal infant growth and development and maternal-infant bonding. A focus on a function-based approach to care in addition to optimization of non-pharmacologic care, including a low stimulation environment, swaddling, clustered care and the provision of mother’s own milk coupled, when possible, with infant caregiver engagement to provide skin-to-skin care, and on demand breastfeeding has been shown to be effective as first-line treatment for infants with NOWS and is endorsed by the American Academy of Pediatrics (AAP) [1].

If non-pharmacologic care alone does not mitigate the severity of opioid withdrawal, pharmacologic treatment is indicated. The traditional approach to pharmacologic treatment for infants with NOWS is initiation and escalation of opioid treatment until symptoms are controlled followed by a slow opioid taper. This approach has been shown to be efficacious but is associated with extended opioid courses and prolonged hospitalization, both of which have been associated with suboptimal developmental outcomes. The use of *pro re nata* (PRN) or symptom-based dosing has been evaluated as a way to decrease postnatal pharmacologic exposure for infants with NOWS. Conceptually, a symptom-based approach would allow control of symptoms for infants who have severity of disease that borders on the usual trigger for the extended opioid treatment protocol. One to three doses of an opioid in such infants may be enough to control symptoms sufficiently and allow for non-pharmacologic therapies to be the primary mechanism for symptom control. This approach could avoid a prolonged course of opioids and weaning for a subset of infants with milder disease, but as an emerging approach it has not been validated. Quality improvement (QI) initiatives conducted in single centers and small regional collaboratives have demonstrated a decrease in the duration of pharmacologic treatment and the length of hospital stay with the use of a symptom-based approach as compared to an opioid taper approach. Improved short-term outcomes with a symptom-based dosing approach to pharmacologic treatment have been noted in infants assessed and managed with either the Eat, Sleep, and Console approach (ESC) or the Finnegan Neonatal Abstinence Assessment Tool (FNAST) [2–5]. In addition, the rate of readmission within 30 days of hospital discharge, a balancing measure used in the QI initiatives, was not increased with a symptom-based dosing approach when compared to a scheduled opioid taper.

QI initiatives have demonstrated a decrease in postnatal opioid exposure and the length of hospital stay with the use of a symptom-based dosing approach and have not found an increase in short-term adverse outcomes during the first month of life. As QI initiatives have been limited to single center or small regional collaboratives, and longer-term developmental outcomes have not been assessed, the efficacy, safety, and generalizability of a symptom-based dosing approach remains unknown and warrants evaluation with a multi-center randomized clinical trial.

#### Rational for selection of study intervention

The overarching hypothesis to be tested is if the use of a symptom-based dosing approach will lead to a reduction in the time until infants are medically ready for discharge when compared to a scheduled opioid taper approach. In the scheduled opioid taper approach, all patients who reach a symptom threshold will be treated with a study site’s usual pharmacologic treatment algorithm. Each algorithm is responsive to symptom severity to allow dosing escalation. All infants follow a protocolized weaning of opioid dose as prescribed by a study site’s pharmacologic treatment algorithm. The theoretic advantage of this approach is that infants with uncontrolled symptoms have a rapid dose escalation with rapid control of NOWS symptoms. The potential disadvantage is that infants are shunted into a treatment approach with denser opioid treatment than they may require for optimal symptom control, with an associated prolongation of hospital stay. The symptom-based approach allows for up to three individual doses in any 24-h period before beginning a scheduled dosing protocol. The theoretic advantage to this approach is that one to three single doses may be enough to control symptoms without requiring a fixed and prolonged regimen. A potential disadvantage is that this approach may delay the start of scheduled opioid dosing in some infants, which may ultimately increase the duration of hospitalization. It is also unclear if the number of infants treated, as defined as receipt of a single dose of opioid, will differ between the two groups. Quality improvement work suggests that clinicians may be more likely to give a single dose for infants with less severe symptoms rather than waiting until symptoms meet the typical thresholds for the initiation of an opioid taper, possibly leading to a greater proportion of infants treated at study sites using a symptom-based protocol.

The scheduled opioid taper approach is traditional management for infants with NOWS; it was developed empirically in the 1970 s and is widely used in clinical care. The symptom-based approach has emerged more recently as part of QI efforts to further tailor care specifically to the infant. The symptom-based approach has been employed entirely in the context of QI programs and efficacy has not been rigorously tested in a controlled fashion. For this reason, there is true equipoise between the two approaches, and both are used at high-quality academic and community hospitals.

Both approaches are currently used, with local variation in the type of primary opioid (methadone, morphine, and buprenorphine), starting dose, maximum opioid dose, weaning rate, cessation dose, and choice of secondary adjunctive medication for more severe cases (phenobarbital or clonidine). This study will employ a comparative effectiveness approach, in which each study site will continue to use its usual care for the primary opioid, dosing regimen, and secondary medication. The rationale for this pragmatic approach is that the overarching question of scheduled or symptom-based dosing is of prime importance and has a larger impact than any site-specific regimen. As all protocols are responsive to individual patient symptoms, the impact of minor differences between study sites will likely not impact the overall comparison. The use of a crossover design will minimize the inter-site differences on the primary comparison. Lastly, the comparative effectiveness paradigm will foster site acceptance and recruit a wider swath of hospital types and patient populations, enhancing the generalizability of the study findings.

## Study hypothesis and objectives

### Primary hypothesis

The length of time from birth until medically ready for discharge will be shorter in infants with NOWS who are ≥ 36 weeks’ gestation, at risk for pharmacologic treatment, and managed for NOWS with a symptom-based dosing approach than in infants with NOWS who are ≥ 36 weeks’ gestation, at risk for pharmacologic treatment, and managed for NOWS with a scheduled opioid taper approach.

The primary hypothesis will be separately tested in two populations:Infants who were assessed and managed with ESC (primary objective)Infants who were assessed and managed with FNAST (secondary objective #1)

### Primary objective

To compare the length of time from birth until medically ready for discharge between infants with NOWS who are ≥ 36 weeks’ gestation, at risk for pharmacologic treatment, who are assessed and managed with ESC, and managed for NOWS with either a symptom-based dosing approach or a scheduled opioid taper approach.

### Secondary hypothesis

All enrolled infants:To compare the length of time from birth until medically ready for discharge between infants with NOWS who are assessed and managed with FNAST and managed for NOWS with either a symptom-based dosing approach or a scheduled opioid taper approachTo compare the receipt of pharmacologic treatment for NOWS between infants managed for NOWS with either a symptom-based dosing approach or a scheduled opioid taper approachTo compare the length of hospital stay between infants managed for NOWS with either a symptom-based dosing approach or a scheduled opioid taper approachTo compare safety outcomes during the first 3 months of life between infants with NOWS who were managed with either a symptom-based dosing approach or a scheduled opioid taper approach

All enrolled infants who were pharmacologically treated:5.To compare the total number of opioid doses administered between infants with NOWS who were pharmacologically treated with either a symptom-based dosing approach or a scheduled opioid taper approach6.To compare the receipt of secondary medications between infants with NOWS who were pharmacologically treated with either a symptom-based dosing approach or a scheduled opioid taper approach7.To evaluate the proportion of infants with NOWS who were initially pharmacologically treated with a symptom-based dosing approach but transitioned to a scheduled opioid taper due to persistent signs of withdrawal8.To evaluate the proportion of infants with NOWS who were initially pharmacologically treated with a scheduled opioid taper but stopped treatment due to excessive sedation or respiratory depression9.To compare safety outcomes during the first 3 months of life between infants with NOWS who were pharmacologically treated with either a symptom-based dosing approach or a scheduled opioid taper approach

## Study design

### Description of study design

The study design is a two-period cluster crossover study design which groups study sites into clusters and randomly assigns each cluster to one of two sequences (i.e., 5-week run-in followed by scheduled opioid taper approach for 5 months (period 1) followed by a 3-week washout followed by symptom-based dosing approach for 5 months (period 2) or 5-week run-in followed by symptom-based dosing approach for 5 months (period 1) followed by a 3-week washout followed by scheduled opioid taper approach for 5 months (period 2)) (see Fig. 1). The duration of each period is expected to be 5 months; this length may need to be modified to ensure sample size is met in Finnegan and ESC groups. Each study site will use the same assessment and management approach (i.e., FNAST or ESC) and will not vary their preferred opioid for primary treatment or alter their pharmacologic treatment algorithm throughout the entire duration of the study.

**Fig. 1 Fig1:**
[figure not shown]
Two-period crossover study design

#### Study intervention

The interventions for this study, the scheduled opioid taper approach and the symptom-based dosing approach (see Fig. 2), were chosen as they are both being utilized as a clinical approach to the pharmacologic treatment for infants with NOWS, yet no generalizable evidence is available to support efficacy or safety of one approach over the other.

**Fig. 2 Fig2:**
[figure not shown]
Dosing approach graphic

##### Intervention description

Throughout this study, all study sites will utilize their assigned dosing approach for the management of all infants with NOWS who meet the threshold for the initiation of opioid treatment as defined by each study site’s pharmacologic treatment algorithm and will transition their dosing approach per their randomized allocation. All study sites will adhere to minimum initial and maximum daily doses of opioids.

Scheduled opioid taper approach:During this approach to care, all enrolled infants with NOWS at the study site will be treated with the study site’s usual scheduled opioid taper approach, as detailed in each study site’s treatment algorithm, if they meet the study site’s withdrawal threshold for pharmacologic treatment.Each study site will utilize their preferred opioid (i.e., morphine, methadone, buprenorphine) and their usual scheduled opioid taper algorithm, as long as the study site’s algorithm meets the parameters established by the protocol study team.Weaning of opioid medications will be per the study site’s scheduled taper and hospital discharge will be per the study site’s usual practice.All infants will be monitored off opioid medications for worsening signs of withdrawal prior to hospital discharge as per the study site’s usual clinical practice.

Symptom-based dosing approach:During this approach to care, all enrolled infants with NOWS at the study site will be treated with the symptom-based dosing approach if they meet the withdrawal threshold for pharmacologic treatment.Each study site will utilize their preferred opioid (i.e., morphine, methadone, buprenorphine) and a symptom-based dosing approach to pharmacologic treatment.Infants with NOWS may receive up to 3 doses of the study site’s preferred opioid during any 24-h period to treat signs of withdrawal once the threshold for pharmacologic intervention is met.The opioid dose used during this approach is the initial opioid dose on each site’s pharmacologic treatment algorithm. The minimum duration between symptom-based doses will be determined by the opioid type used at the study site. Examples are provided in the dosing approach graphic below. If an infant meets the threshold for pharmacologic treatment at the minimum dosing interval for the type of opioid used at the site (i.e., short interval dosing) across two assessment periods, the infant will move to the schedule opioid algorithm at the first up titration dose (with the third dose of opioid medication). The need for recurrent dosing at the minimum duration threshold suggests that the severity of opioid withdrawal is unlikely to be well controlled with symptom-based dosing and early transition to scheduled opioid treatment would better support the physiologic needs of the infant.If a 4th dose is required within any 24-h period, the study site will move to scheduled opioid treatment per the algorithm used at the study site to complete the infant’s pharmacologic treatment. The 4th dose would include the first up titration of the study site’s scheduled dosing protocol.If opioid dosing is scheduled, weaning of opioid medications will be per the study site’s scheduled taper and hospital discharge will be per the study site’s usual practice.During this approach, it is recommended that all infants be monitored off opioid medication for worsening signs of withdrawal for ≥ 48 h prior to hospital discharge.

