### Primary endpoint

Time from birth until infant meets criteria for medically ready for discharge (days). An infant is considered medically ready for discharge when they are discharged by the medical provider or when they meet both of the following criteria:≥96 h of age≥48 h since last dose of opioid treatment (i.e., morphine, methadone, or buprenorphine)

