#### Analyses of secondary objectives

Using the model outlined in the Analysis plan section, Table 4 provides a summary of the endpoint, analysis population, statistical model, and resulting estimate for each of the secondary objectives.

**Table 4 Tab4:** Statistical approach to be used for secondary objectives

Objective	Endpoint	Analysis population	Model	Estimate
Secondary objective #1	Number of days from birth until the participant meets criteria for medically ready for discharge	ITT (FNAST infants only)	GLMM • Distribution: negative binomial • Link function: log	Similar to the Primary analysis of primary objective section
Secondary objective #2	Receipt of pharmacologic treatment	ITT	GLMM • Distribution: binary • Link function: log	Adjusted risk of receipt of pharmacologic treatment for NOWS in infants managed with a symptom-based dosing approach Adjusted risk of receipt of pharmacologic treatment for NOWS in infants managed with a scheduled opioid taper approach Adjusted relative risk of receipt of pharmacologic treatment for NOWS between infants managed with a symptom-based dosing approach to infants managed with a scheduled opioid taper approach
Secondary objective #3	Number of days from birth until hospital discharge	ITT	GLMM • Distribution: negative binomial • Link function: log	Adjusted mean number of days until hospital discharge in infants managed with a symptom-based dosing approach Adjusted mean number of days until hospital discharge in infants managed with a scheduled opioid taper approach Difference in the adjusted mean number of days until hospital discharge between infants managed with a symptom-based dosing approach and infants managed with a scheduled opioid taper approach Adjusted RR of days until hospital discharge between infants managed with a symptom-based dosing approach to infants managed with a scheduled opioid taper approach
Secondary objective #4	• Inpatient composite safety outcome • Inpatient critical safety outcome • Outpatient composite safety outcome • Outpatient critical safety outcome	ITT	Descriptive statistics	Percentage of infants who met each endpoint will be summarized by study intervention

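### The off-opioid observation instruction before discharge differs by arm: it enters length of stay directly, and the primary endpoint only where a site's usual wait is under 48 h

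*Protocol article*

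**What the plan says.** In the protocol article, Intervention description, the scheduled taper list says that infants are "monitored off opioid medications for worsening signs of withdrawal prior to hospital discharge as per the study site’s usual clinical practice". No duration is given. The symptom-based list says that, during that approach, "it is recommended that all infants be monitored off opioid medication for worsening signs of withdrawal for ≥ 48 h prior to hospital discharge".

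The symptom-based list also covers infants who move on to scheduled dosing. For them, "hospital discharge will be per the study site’s usual practice". This comes immediately before the 48 h recommendation for all infants, and the article does not say which of the two governs these infants.

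Under Primary endpoint, an infant is ready "when they are discharged by the medical provider or when they meet both of the following criteria": at least 96 h of age, and at least "48 h since last dose of opioid treatment". Table 3 repeats this definition. Secondary objective #3 is the "Number of days from birth until hospital discharge" and carries no time criterion.

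The rationale for the study intervention and Measures to minimize bias both rely on the crossover to handle differences between sites. Neither mentions the difference in observation instruction.

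**The concern.** The stated question is how the opioid is dosed, scheduled or by symptoms. If one arm also carries a stated minimum observation time and the other does not, the comparison has a second component. A crossover cancels what stays constant within a site. This instruction changes at the same moment as the treatment, so it does not cancel.

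Length of stay absorbs any difference in observation time. The primary endpoint can be reached through the provider-discharge clause. At a site that usually discharges sooner than 48 h after the last dose, a taper infant is counted at discharge. A symptom-based infant managed as recommended is counted at 48 h. Part of a real benefit of symptom-based dosing could then be hidden.

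**Working it through.** **The plan's own figures.** Inputs from Sample size considerations and Table 5: ESC 16 sites, taper mean 10.5 days, over-dispersion 5.5; FNAST 8 sites, taper mean 16.5 days, over-dispersion 8.4; both with 10 infants per site per period, ICC 0.15, exchangeable correlation, a t-distribution and two-sided 0.05.

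Var(log RR) = φ × (1/m1 + 1/m2) × (1 − ICC) / (sites × 10), with 2 × sites − 2 degrees of freedom.

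- ESC, 10.5 vs 8.3: 5.5 × 0.2157 × 0.85 / 160 = 0.00630, SE 0.0794, power 81.7% (plan 80%). For 8.0 days: 90.6% (plan 90%).
- FNAST, 16.5 vs 11.7: 8.4 × 0.1461 × 0.85 / 80 = 0.01304, SE 0.1142, power 79.9% (plan 80%). For 11.0 days: 90.0% (plan 90%).

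The plan's figures reproduce within 2 points.

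**How the endpoint behaves.** For a treated infant the definition amounts to

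readiness = min(discharge, max(96 h of age, last dose + 48 h)).

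If the site's usual wait w is 48 h or more, the criteria are met no later than discharge in either period, and the instruction cannot move the endpoint. If w is below 48 h, the taper infant can be counted at discharge and the symptom-based infant up to 48 − w hours later. The shift can only lengthen the symptom-based arm.

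**Size.** Shift in the arm mean (days) = treated share × fraction of treated infants affected × (48 − w)/24.

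The treated shares are the INFORM NOW figures in the article: 39.1% for ESC and 78.8% for FNAST. The detectable differences at 80% power are 10.5 − 8.3 = 2.2 days and 16.5 − 11.7 = 4.8 days. The article does not give w or the fraction affected, so both are assumptions.

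| Group | w | Fraction affected | Shift (days) | % of detectable difference | RR observed | Power |
|---|---|---|---|---|---|---|
| ESC | 48 h | any | 0 | 0 | 0.79 | 82% |
| ESC | 36 h | 100% | 0.391 × 0.5 = 0.20 | 9% | 0.81 | 74% |
| ESC | 24 h | 10% | 0.391 × 0.1 = 0.04 | 2% | 0.79 | 80% |
| ESC | 24 h | 100% | 0.391 × 1 = 0.39 | 18% | 0.83 | 64% |
| FNAST | 48 h | any | 0 | 0 | 0.71 | 80% |
| FNAST | 36 h | 100% | 0.788 × 0.5 = 0.39 | 8% | 0.73 | 72% |
| FNAST | 24 h | 10% | 0.788 × 0.1 = 0.08 | 2% | 0.71 | 79% |
| FNAST | 24 h | 100% | 0.788 × 1 = 0.79 | 16% | 0.76 | 63% |

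For a given w, the 100% rows are upper bounds: every site waits only w hours and the recommendation is followed in full. They also count infants moved to scheduled dosing. If usual practice governs those infants, the instruction creates no arm difference for them.

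With no true effect, the 24 h upper bound gives an apparent RR of (10.5 + 0.391)/10.5 = 1.04 in ESC and (16.5 + 0.788)/16.5 = 1.05 in FNAST.

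**The case against.** The strongest defence is that the primary endpoint is largely protected. The 96 h and 48 h criteria are the same in both arms, and no statement in the article shows any site discharging treated infants sooner than 48 h after the last dose. The consent-waiver section says the primary outcome was built on professional-body recommendations to support safe discharge of all infants. The 48 h is a recommendation, so adherence may be partial. The trial is also a pragmatic comparison of care approaches, and a stated minimum in the newer arm could be part of that approach.

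Most of this stands as a limit on size. It does not answer the point about length of stay, which has no common criterion. The article also does not say that the observation minimum belongs to the strategy under comparison.

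Some stronger readings are tempting but unsupported:

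- A reader might infer that the primary endpoint is biased as a matter of course. It is not: with usual waits of 48 h or more the shift is zero.
- A reader might infer that length of stay can be pushed either way. The recommendation is a minimum, and nothing tells a site with a longer wait to shorten it.
- A reader might infer that a null result could not be interpreted. Dose and discharge times are collected, so the interval can be examined directly.

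It is also fair that enrollment was expected to end in April 2025, so rewording may come too late to change conduct. The analytic remedy does not depend on rewording.

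**Conclusion.** The arms carry different off-opioid observation instructions, and the symptom-based list is unclear about infants moved to scheduled dosing. Length of stay contains the interval directly. The primary endpoint is exposed only at sites whose usual wait is under 48 h. There the shift runs against symptom-based dosing, so it can dilute a benefit but cannot create one.

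Over an assumed usual wait of 48 h to 24 h, the primary shift lies between 0 and 0.39 day in ESC and between 0 and 0.79 day in FNAST. The upper ends are bounds, not estimates. They require a 24 h wait at every site, every treated infant affected and full adherence to the recommendation. If 10% of treated infants are affected at 24 h, the ESC shift is about 0.04 day. The true size cannot be found from the article. The case for acting is that the check is cheap.

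**What to change.** 1. Reconcile the two lists under Intervention description, including the bullet on infants moved to scheduled dosing, or state that the difference in observation is a deliberate part of the strategy being compared. Which observation period applies is for the sponsor to decide.
2. Before database lock, pre-specify a supportive analysis of the primary endpoint, not a replacement. In treated infants of both arms, compute readiness as the later of 96 h of age and 48 h after the last recorded opioid dose, without the provider-discharge clause. Handle infants discharged on opioid separately: the site exclusion applies only where this is routine (10% or more), and doses are recorded only up to discharge, so their final dose is unknown.
3. Beside secondary objective #3, report the interval from last opioid dose to discharge by arm. This shows how much of any length-of-stay difference is observation time.

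Cost: a short text change, one extra model fit and one descriptive table. Each opioid dose before discharge and the date and time of discharge are already collected. The downside is that, for infants discharged early, the formula gives a readiness time later than actual discharge, which is why it should only support the primary analysis.
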